## Introduction

Polycystic ovary syndrome (PCOS) is a common gynecological endocrine disorder with an incidence rate of 5%-18% [1–3]. Globally, approximately 60% of PCOS women are accompanied by overweight or obesity [4]. Previous studies have shown that overweight and obesity are significant risk factors for women with PCOS [5,6]. Overweight and obese women with PCOS amplify conception challenges and lower assisted reproductive technology success rates, while also heightening risks of cardiovascular disease, diabetes, and mental health issues like anxiety and depression [7–10]. Consequently, weight loss is vital for PCOS women to restore fertility, prevent chronic diseases, and enhance their overall well-being [11]. Among weight reduction strategies, dietary intervention stands out as a key management approach [12]. Numerous dietary interventions for PCOS treatment have been suggested, including low-calorie [13], low-carbohydrate [14], low-glycemic index [15], Mediterranean [16], and ketogenic diets [17]. However, these methods face challenges, including adherence, metabolic adaptation, and psychological strain [18]. Time-restricted eating (TRE), an emerging eating pattern, focus on limiting daily eating to specific periods, while completely avoiding calorie-containing intakes during the rest of the day [19]. TRE effectively reduces body weight, lowers blood sugar levels, and improves insulin sensitivity and metabolism by controlling the duration and timing of food intake [20]. Different durations and windows of food intake yield varying effects. 4-hour and 6-hour eating windows reduced patients’ weight and improved cardiometabolic health, but adverse effects such as nausea, headaches, and constipation are reported [21,22]. 10-hour and 12-hour eating windows did not significantly affect weight loss or insulin sensitivity improvement [23–25]. The 8-hour TRE window is most extensive, but results vary based on the specific eating window. Neither too early nor too late time window can achieve the desired effect, or even have a negative impact [26–28]. At present, the time window of 8:00–16:00 works best, which, according to some studies, is consistent with the human body’s circadian rhythm [29–31].

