#### Inclusion criteria

(1) age 18–49 years old; (2) a diagnosis of PCOS according to the Rotterdam criteria [40]; (3) BMI ≥ 24 kg/m^2^ (where BMI between 24–27.9kg/m^2^ is overweight, BMI > 28kg/m^2^ is obese); (4) willing to sign a consent form.

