#### Exclusion criteria

(1) the participant has used weight loss drugs or hormone therapy in the past six months; (2) body weight fluctuation > 5% in the past three months; (3) on pregnancy, breastfeeding, preparation for pregnancy or perimenopausal period; (4) regular high-intensity exercise or night shifts due to work; (5) serious heart disease or stroke (including myocardial infarction, unstable angina, heart bypass surgery, PTCA, congestive heart failure, and ischemic heart disease) within six months; (6) participants with other diseases (such as primary amenorrhea, thyroid dysfunction, malignant tumors, diabetes, severe gastrointestinal, renal or liver diseases); (7) history of hypotension; (8) participants who have undergone bariatric surgery or have been diagnosed with cancer.

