### Procedures and measures

#### Baseline investigation and development of calorie restriction program

Before the formal trial begins, all potential participants will undergo a 1-week baseline survey. Baseline surveys are designed to confirm participants’ eligibility for the study, assess their interest in the study, and obtain informed consent. At the same time, a series of baseline measures will be taken, such as weight, BMI, body composition, sex hormones, glucose and lipid metabolism indicators, as well as quality of life assessment, sleep quality assessment, anxiety and depression assessment. In addition, a weekly dietary assessment will be conducted using food journals and food photographs to record in detail the participants’ daily eating patterns, food intake and calorie intake. Work intensity and basal metabolic rate will be assessed using the International Physical Activity Questionnaire and a basal metabolic meter, respectively. Based on these assessments, the daily calorie requirements for each participant will be calculated. In the personalized calorie restriction program, each participant will be required not to exceed their individual daily calorie needs and will have the autonomy to decide the types and quantities of food they consume, while ensuring that the overall calorie goal is met.

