#### TRE group

In addition to following a personalized calorie restriction regimen based on baseline survey assessment results, TRE participants will be instructed to consume their allotted calories within a specific eight-hour time window (8 a.m. to 16 p.m.). During this time, they will have autonomy to decide the specific types and amounts of food they consume, while adhering to their overall calorie targets. Outside of this eight-hour window, participants will be in a fasting state and only allowed to consume sugar-free water and zero-calorie beverages to meet their basic fluid needs. This means that TRE participants will effectively be fasting for 16 hours each day (from 16 p.m. to 8 a.m. the next day).

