#### Support and follow-up

To ensure the effective implementation of the intervention and the accuracy of the data, we provided full support and close follow-up for all participants. First, all participants will receive personalized dietary counseling provided by a professional nutritionist. These consultations cover not only the development of meal plans, but also specific guidance on how to carry out these plans in real life. Participants will receive a detailed diet information booklet at the hospital with precise portion size recommendations, sample menus, and practical tips on how to properly schedule meals within a specific time window. In addition, we asked participants to keep a detailed food diary and to take photographs before and after each meal. This practice was designed to help participants better monitor their eating habits, while also providing us with an accurate source of data to assess when they ate and how much food they consumed.

In terms of follow-up, we have developed a strict monitoring plan. During the intervention, two researchers will contact the participants weekly by phone, not only focusing on their diet implementation, but also asking in detail and recording any possible adverse events (such as hunger pangs, dizziness, mood swings, etc.). For any questions or confusion encountered, the researchers will provide timely answers and necessary guidance to ensure participants’ compliance and the smooth conduct of the study. At the same time, participants’ food diaries and food photos will be regularly reviewed, using Chinese food composition lists to accurately assess their nutrient intake [41]. This step is essential to verify the implementation of the diet plan and adjust the diet regimen.

Our follow-up did not stop after the intervention. Instead, we will continue to contact participants by phone on a monthly basis to check on their weight changes and encourage them to share any new developments regarding their diet, lifestyle habits, or health status. This long-term follow-up mechanism will help us evaluate the long-term effects of time-restricted dietary interventions and provide valuable data to support future studies. Fig 1 shows the schedule for enrolment, intervention and assessment as required by SPIRIT.

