Scale	Pittsburgh Sleep Quality Index			The Pittsburgh Sleep Quality Index (PSQI) was used to rate participants’ sleep quality. It consists of 19 self-assessment entries and 5 other-assessment entries, in which the 19th self-assessment entry and 5 other-assessment entries are not involved in scoring. 18 entries form 7 components, each component is scored on a 0–3 scale, and the cumulative score of each component is the total PSQI score, which ranges from 0–21, with higher scores indicating poorer sleep quality.		Baseline, 4^th^ week, 8^th^ week, 12^th^ week
	SF-36			Sf-36 consists of eight dimensions: vitality (VT), mental health (MH), physiological function (PF), physiological function (RP), emotional function (RE), physical pain (BP), social function (SF), and general health (GH). The 8 dimensions get their own dimension score according to their own entry score, and the health change score is not included in the total score. The total quality of life score is the sum of eight dimensions, and the higher the total score, the better the quality of life.		
	Hospital Anxiety and Depression Scale			Hospital Anxiety and Depression Scale (HADS) was used to assess the degree of anxiety and depression of the participants, including two subscales, Hospital Anxiety and Depression Scale-Anxiety (HADS-A) and Hospital Anxiety and Depression Scale-Depression (HADS-D), with 7 entries each and a total of 14 entries. Higher scores indicate more severe anxiety or depressive symptoms.		
**Outcome Measure**			**Collection Method/Tool**		**Details**	**Measurement Time Points**
Compliance assessment			*Wechat* app		Compliance will be determined by the number of days participants adhere to the assigned dietary rules. Control group participants will be instructed to limit their caloric intake to the defined daily allotment, while TRE group participants will be consumed within designated mealtimes and meet daily calorie targets. We will employ a combination of methods to monitor compliance, including the use of food diaries and *Wechat* apps that can track meal times, calorie intake, and adherence to dietary rules. To improve participant compliance, each participant will be given a free physical examination and a food scale.	Intervention: baseline, once a week Follou-up: once a month

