Safety assessment*			Asked by the investigator or voluntarily reported by the participant		Investigators will collect, record, and report all adverse events that occur during the trial period (beginning with the participant’s informed consent and ending with the participant’s last assessment, whether asked by the investigator or voluntarily reported by the participant). The participant’s symptoms, severity, onset and duration, treatment, and course of action will be recorded in the original data to evaluate their relevance to the trial intervention, and will be recorded in detail, signed and dated by the investigator. If serious adverse events occur during the clinical trial, the investigator will take appropriate treatment measures for the subjects and record them in the original data, and report them to the principal investigator of the trial center and the ethics committee within 24 hours. Researchers will carefully fill in the serious adverse event report form, and sign and date the report.	

*Safety indicators will include: the overall incidence of adverse events and the incidence of each adverse event; the severity and incidence of various types of gastrointestinal reactions, such as nausea and gastroparesis; the severity and incidence of hypoglycaemic events; early withdrawal due to adverse events; changes in vital signs; the severity and incidence of psychoneurological symptoms such as somnolence, anorexia, and other events.

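### The exclusion criteria do not name eating disorders: a current one is left to the investigator's discretion and a past one is not covered, in a trial built on fasting, calorie limits and photographed meals

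*Protocol article*

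**What the plan says.** Eligibility is given as two complete numbered lists. Inclusion has four items: age, "a diagnosis of PCOS according to the Rotterdam criteria", a BMI of at least 24 kg/m², and consent. Exclusion has eight items. Criterion (6) is the catch-all, for "participants with other diseases (such as primary amenorrhea, thyroid dysfunction, malignant tumors, diabetes, severe gastrointestinal, renal or liver diseases". No item in either list mentions an eating disorder or any psychiatric condition.

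The demands on participants are in these sections:

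- **TRE group:** "TRE participants will effectively be fasting for 16 hours each day". This applies to the TRE arm only.
- **Baseline investigation and development of calorie restriction program:** "each participant will be required not to exceed their individual daily calorie needs". This applies to both arms and is repeated under Control group.
- **Support and follow-up:** all participants are asked to "keep a detailed food diary and to take photographs before and after each meal". This also applies to both arms.

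The safety footnote to Table 1 (Measures) counts "the severity and incidence of psychoneurological symptoms such as somnolence, anorexia, and other events". In the same table HADS "was used to assess the degree of anxiety and depression of the participants", at baseline and at weeks 4, 8 and 12. It has no stated role in eligibility, and no baseline measure asks about disordered eating.

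**The concern.** Limits on eating times and calories, together with close recording of every meal, bear directly on an eating disorder. The exclusion list is detailed enough to name bypass surgery, hypotension and night-shift work, but it does not name the illness most closely tied to what the trial asks women to do. Followed as written, it would let a woman with a past eating disorder be randomised. Two investigators could also reach different decisions on a woman with a current one.

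Two things are at stake. The first is the safety of that woman, in a trial that states safety as an aim. The second is how one of her adverse events is read. Table 1 asks the investigator to judge whether each event relates to the intervention. If an appetite or mood event occurs in a woman whose eating-disorder history was never asked about, that judgement lacks a fact it needs.

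**Working it through.** **Step 1. Does any listed criterion reach an eating disorder?**

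| Case | Closest criterion | Covered? |
|---|---|---|
| Current disorder, underweight | Inclusion (3), BMI at least 24 | Excluded by BMI |
| Current disorder, BMI 24 or more | Exclusion (6), other diseases with examples | Only if the investigator counts it as an other disease |
| Current disorder with recent weight-loss drugs, weight change above 5% or regular intense exercise | Exclusion (1), (2), (4) | Some cases, incidentally |
| Past disorder, now in remission | None; criterion (6) speaks of participants with other diseases | No |

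**Step 2. Which demands differ between the arms?** The fast is in the TRE arm only. The calorie ceiling, diary and photographs are in both. The ceiling is set at calculated daily need, and no deficit is stated.

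**Step 3. How many women might this concern?** The documents give no prevalence, so this is an illustration on an assumed range of 3% to 10%.

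- Arm size, from the Sample size section: N = 2 × (1.96 + 0.84)² × 3.87² / 2.5² = 37.57, rounded up to 38. With 20% dropout, 38 / 0.80 = 47.5, rounded up to 48 per group. The stated 48 is reproduced at 20% dropout.
- Expected number per arm: 0.03 × 48 = 1.4 and 0.10 × 48 = 4.8, so about 1 to 5. Randomisation is 1:1, so the same expectation holds in the control arm.
- Chance of at least one such woman in a given arm: 1 − 0.97^48 = 77% at 3%. At an assumed 1% it is 1 − 0.99^48 = 38%.

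These are counts of women, not of events. The protocol gives no psychoneurological event rate, so no share of events can be derived from them.

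**Step 4. Can the question be asked before allocation?** The article is not consistent on this. Study design and ethics has participants randomised after consent, for a period that begins with the one-week baseline survey. The Baseline investigation section puts that survey before the formal trial, in potential participants, and uses it to confirm eligibility.

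**The case against.** The strongest case against is that criterion (6) is open-ended. An investigator can exclude a current eating disorder under it, so it would be wrong to say such women are simply eligible. That stands, and the point is limited to discretion for a current disorder and silence on a past one.

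A reader might also infer that the protocol contradicts itself by naming psychological strain and anorexia as risks of TRE. It does not. In the Introduction, "these methods face challenges, including adherence, metabolic adaptation, and psychological strain" refers to the low-calorie, low-carbohydrate, low-glycemic index, Mediterranean and ketogenic diets; TRE is introduced after them as something different. In the safety footnote anorexia is a symptom listed beside somnolence, not an eating-disorder diagnosis.

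A reader might further infer that the HADS and SF-36 comparisons are biased. Random 1:1 allocation places affected women in both arms on average, both scales are taken at baseline, and there is a concurrent control arm. What remains is chance imbalance in small arms. Nor do the documents support saying that such women would dominate the event counts, or that their dropout would fall mainly in the TRE arm.

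Monitoring does exist: weekly calls that ask about adverse events including mood swings, nutritionist counselling, and termination for significant safety issues. These act after enrolment and do not replace an entry question.

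**Conclusion.** The point holds as a gap in participant protection and in the attribution of individual events. It does not touch the weight and BMI analysis and implies no systematic bias in the psychological outcomes. Its size cannot be computed from the documents. The figure of about 1 to 5 women in each arm of 48 rests wholly on the assumed 3% to 10%. The conclusion itself needs no prevalence: it rests on the eligibility lists being complete as printed and on the stated demands of the intervention. It is a modest, inexpensive improvement and worth making.

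**What to change.** Add a current or past diagnosed eating disorder to the exclusion criteria. Ask about it in one history question at the eligibility check, answered before the allocation envelope is opened. For that to work, Study design and ethics and the Baseline investigation section must be reconciled on whether the baseline survey precedes randomisation.

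Do not use baseline HADS as the flag. It measures anxiety and depression rather than disordered eating, the protocol gives no threshold for it, and screening on it would select on a secondary outcome.

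The cost is one criterion and one question. A few candidates will be lost, and the result will generalise slightly less widely.

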### Termination criteria

(1) incidence of significant security issues; major and unforeseen adverse events directly linked to the intervention; (2) pregnancy; (3) participants requesting to withdraw their informed consent, showing reluctance to comply with the intervention, or due to other unforeseen reasons.

### Randomization and blinding

In this study, randomization will be achieved using opaque closed envelopes and simple random sampling. Based on sample size estimates, two groups will be allocated to a 1:1 ratio. To ensure an unpredictable distribution, 96 random numbers (either 0 or 1, each making up half) will be generated. These numbers will be written on 96 cards and sealed in yellow-brown envelopes for concealed grouping. After unsealing, participants will be assigned to either the “control group” (0) or the “TRE group” (1) based on the random number on the card. Generating the assignment order, recruiting participants, and assigning participants to the intervention will be performed separately by different researchers in this research group.

This study will be an open-label clinical trial design, and participants cannot be blinded because the intervention plan will limit the time of participant eating. To reduce bias error, blinding of outcome assessors and data analysts will be used to compensate. To achieve this, outcome assessors will undergo training to ensure they conduct evaluations in a standardized and objective manner, free from any influence stemming from knowledge of the participant’s group assignment. Additionally, data analysts will work with anonymized datasets, where all identifying information related to group assignment has been removed. Furthermore, stringent protocols will be enforced to prevent any unauthorized communication among outcome assessors, data analysts, and those responsible for assigning participants to groups or delivering interventions.

### Procedures and measures

#### Baseline investigation and development of calorie restriction program

Before the formal trial begins, all potential participants will undergo a 1-week baseline survey. Baseline surveys are designed to confirm participants’ eligibility for the study, assess their interest in the study, and obtain informed consent. At the same time, a series of baseline measures will be taken, such as weight, BMI, body composition, sex hormones, glucose and lipid metabolism indicators, as well as quality of life assessment, sleep quality assessment, anxiety and depression assessment. In addition, a weekly dietary assessment will be conducted using food journals and food photographs to record in detail the participants’ daily eating patterns, food intake and calorie intake. Work intensity and basal metabolic rate will be assessed using the International Physical Activity Questionnaire and a basal metabolic meter, respectively. Based on these assessments, the daily calorie requirements for each participant will be calculated. In the personalized calorie restriction program, each participant will be required not to exceed their individual daily calorie needs and will have the autonomy to decide the types and quantities of food they consume, while ensuring that the overall calorie goal is met.

#### Control group

Participants in the control group will maintain their original eating habits, but will follow a personalized calorie restriction regimen based on baseline survey evaluation results. This means their daily calorie intake will be strictly controlled to ensure they do not exceed the upper limits set out in the programme, promoting healthy weight management. The control group, however, did not undergo a specific TRE intervention, but received regular telephone follow-up visits from researchers to monitor their eating habits and weight changes.

#### TRE group

In addition to following a personalized calorie restriction regimen based on baseline survey assessment results, TRE participants will be instructed to consume their allotted calories within a specific eight-hour time window (8 a.m. to 16 p.m.). During this time, they will have autonomy to decide the specific types and amounts of food they consume, while adhering to their overall calorie targets. Outside of this eight-hour window, participants will be in a fasting state and only allowed to consume sugar-free water and zero-calorie beverages to meet their basic fluid needs. This means that TRE participants will effectively be fasting for 16 hours each day (from 16 p.m. to 8 a.m. the next day).

#### Support and follow-up

To ensure the effective implementation of the intervention and the accuracy of the data, we provided full support and close follow-up for all participants. First, all participants will receive personalized dietary counseling provided by a professional nutritionist. These consultations cover not only the development of meal plans, but also specific guidance on how to carry out these plans in real life. Participants will receive a detailed diet information booklet at the hospital with precise portion size recommendations, sample menus, and practical tips on how to properly schedule meals within a specific time window. In addition, we asked participants to keep a detailed food diary and to take photographs before and after each meal. This practice was designed to help participants better monitor their eating habits, while also providing us with an accurate source of data to assess when they ate and how much food they consumed.

In terms of follow-up, we have developed a strict monitoring plan. During the intervention, two researchers will contact the participants weekly by phone, not only focusing on their diet implementation, but also asking in detail and recording any possible adverse events (such as hunger pangs, dizziness, mood swings, etc.). For any questions or confusion encountered, the researchers will provide timely answers and necessary guidance to ensure participants’ compliance and the smooth conduct of the study. At the same time, participants’ food diaries and food photos will be regularly reviewed, using Chinese food composition lists to accurately assess their nutrient intake [41]. This step is essential to verify the implementation of the diet plan and adjust the diet regimen.

Our follow-up did not stop after the intervention. Instead, we will continue to contact participants by phone on a monthly basis to check on their weight changes and encourage them to share any new developments regarding their diet, lifestyle habits, or health status. This long-term follow-up mechanism will help us evaluate the long-term effects of time-restricted dietary interventions and provide valuable data to support future studies. Fig 1 shows the schedule for enrolment, intervention and assessment as required by SPIRIT.

